### Participant timeline

The participant timeline is displayed in Table 1 schedule of activities.

**Table 1 Tab1:** Schedule of activities

Study phase	Screening/consent	Baseline/randomisation	Treatment period (PTA)	Post-PTA	Discharge	Three-month follow-up
ACD/ MTDM identification	X					
Trial introduction	X					
MTDM consent	X					
Screening	X					
Participant consent				X		
Randomisation		X				
Demographics^a^		X		X		
Medical record^b^		X	X		X	
Medical information^c^		X	X	X		
Blood test(s)^d^		X	X	X		
WPTAS		X	X			
ABS		X	X	X	X	
Simpson-Angus Scale		X	X			
Administer treatment			X			
Treatment log			X			
AE monitoring^e^			X			
RAVLT				X		
SDMT				X		
SF-12				X	X	X
FIM				X	X	
MPAI-4						X
PDHSUQ						X

^a^Age, gender, years of education, marital status, pre-injury employment/study status, drug and alcohol history, psychiatric history

^b^One or more of date and cause of injury, Glasgow Coma Scale, PTA duration, imaging results, surgical intervention, other injuries, Injury Severity Score, therapy hours and number of sessions, special nursing care, medication details, number of patients on ward

^c^Weight, BP, HR, WC

^d^Assessing fasting lipids, fasting glucose, HBA1C, creatinine

^e^Respiratory issues, lethargy, nausea, vomiting, difficulty swallowing, constipation, urinary retention, dizziness, seizures

#### Baseline—day 0

Following eligibility confirmation and randomisation, the following information will be gathered from the participant’s medical record: baseline WPTAS and ABS, demographic information (age, gender, years of education, marital status, pre-injury employment/study status, drug and alcohol history and psychiatric history) and medical information (date and cause of injury, Glasgow Coma Scale score, PTA duration, imaging results, surgical intervention, other injuries, injury severity score, therapy hours, special nursing care and medication details). Pre-treatment measures of weight, blood pressure (BP), heart rate (HR) and waist circumference (WC) will be conducted by nursing staff. Blood tests assessing fasting lipids, fasting glucose, haemoglobin A1c (HBA1C) and creatinine will be conducted. The Simpson-Angus Scale (SAS; [49]) will be completed by the patient’s treating physiotherapist, in order to assess the presence of extrapyramidal symptoms.

#### Treatment—day 0 until emergence from PTA (or 6 months maximum)

The treatment period will last from day of completion of baseline assessments until the patient is deemed to have emerged from PTA or until 6 months have elapsed. Emergence from PTA is defined as the first of three consecutive days on which a score of 12/12 on the WPTAS is achieved. Participants will be administered their randomised dose. They will also receive optimal environmental management as per guidelines [7]. WPTAS and ABS scores will be recorded by nursing staff or the patient’s clinical neuropsychologist. Need for dosage escalation and rescue medication use will be monitored by study staff. To describe concomitant care and inform health-economic evaluation, the number of patients on the ward, therapy hours and number of sessions and medication use including name and dose regimen will be recorded from the participant’s medical file.

AE monitoring will occur weekly. Clinically significant changes in these parameters will be recorded as AEs and a decision made by the treating doctor in consultation with a psychiatrist and the DSMC as to whether serious AEs necessitate withdrawal from the study.

#### Post-PTA—3 days following emergence from PTA (or 6 months)

Study staff will be informed by ABI ward staff when participants emerge from PTA and treatment will be titrated down as appropriate. Participant consent will be sought as soon as possible following emergence from PTA. Study staff will ask the participant to provide any demographic information unable to be gained from their medical record. Post-PTA measures of weight, BP, HR, WC and blood tests assessing fasting lipids, fasting glucose, HBA1C and creatinine will be conducted. The ABS will be completed daily for 2 weeks following emergence from PTA. Cognitive performance will be measured using the Rey Auditory Verbal Learning Test (RAVLT; [50]) and Oral Symbol Digit Modalities Test (SDMT; [51]). Functional independence will be measured using the Functional Independence Measure (FIM; [52]) and the 12-Item Short Form Health Survey Version 2 (SF-12; [53, 54]). These measures will be completed within 2 weeks of emergence from PTA. If participants remain in PTA at 6 months, treatment will be ceased and measures of weight, BP, HR, WC and blood tests will be administered at this time point. Remaining measures corresponding to the post-PTA time point will be administered upon the participant’s emergence from PTA.

#### Discharge

Study staff will be notified by ABI ward staff when the participant is ready to be discharged from Epworth HealthCare. Within 1 week prior to hospital discharge, any additional medical information not previously available in the participant’s medical record will be gathered, the ABS will be completed and functional independence will be measured using the FIM and the SF-12.

#### Three-month post-discharge follow-up

Participants and their MTDM will be contacted at 3 months post-discharge via telephone. Participants will complete the SF-12, their MTDM will complete the Mayo Portland Adaptability Inventory-4 (MPAI-4; [55]) and both parties will complete the Post-Discharge Health Service Utilisation Questionnaire (PDHSUQ). These measures will be completed within 3 weeks of the calculated follow-up date.

The participant’s MTDM may not be in a position to answer the questions posited in the MPAI-4 and PDHSUQ (for example, if they live in different countries or do not have a close relationship). In such cases, researchers will ask the participant to nominate another party who the researchers may contact to gather this information. Participants will be thanked for their participation and debriefed, including answering of any questions they might have regarding the study.

### Concomitant and post-trial care

All participants will receive environmental management designed to minimise agitation [7] including being located in a secure and quiet ward, avoiding restraint and overstimulation, allowing frequent rest and regulation of visitors to avoid overstimulation. Dedicated, consistent staff will optimise communication, reassurance and orientation. Participants will be permitted to engage in whatever other medical, rehabilitative or pharmacological therapy their medical team deems appropriate. Exceptions to this allowance include the use of medications for agitation (not including trial or rescue medication).

Following completion of the study, participants will continue to receive usual rehabilitation and other services as offered by Epworth HealthCare. Epworth HealthCare will also provide treatment for any drug-related AEs.

### Outcomes and measures

#### Primary outcome

To assess the efficacy of the atypical antipsychotic olanzapine in reducing agitation in patients in PTA following TBI over and above recommended environmental management, we will examine the difference between active and placebo groups’ mean daily score on the ABS during PTA. This outcome will include all daily ABS assessments throughout the treatment period. The ABS is a widely used measure of agitated behaviour in TBI [56–58]. Completion involves the observer rating the presence of 14 agitated behaviours based on the past 8-h period. Internal consistency is high, and construct validity and inter-rater reliability have been established [57–60]. Nurses and clinical neuropsychologists who complete the ABS at Epworth HealthCare are trained in its use.

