### Intervention, randomisation and allocation

Treatment will be administered by ward staff orally in capsule form. Study product may also be administered via nasogastric or percutaneous endoscopic gastrostomy (PEG) tube. Each active capsule will contain 5 mg olanzapine and 137.5 mg Flocel (filler). Placebo capsules will contain 142.5 mg Flocel (filler). Dosage will be flexible and titrated as follows: (1) one capsule at night (5 mg olanzapine or matching placebo per day); (2) one capsule in the morning, one capsule at night (10 mg olanzapine or matching placebo per day); (3) one capsule in the morning, two capsules at night (15 mg olanzapine or matching placebo per day); and (4) two capsules in the morning, two capsules at night (20 mg olanzapine or matching placebo per day). Dosage may be escalated every 3 to 4 days. The decision to escalate dose will be made based on whether ABS score reduces between dose escalation days, the clinical appropriateness of dose escalation and whether that participant’s ABS score is in the agitated range (ABS > 21). Should a participant’s ABS score fall below the agitated range (ABS < 22) whilst in PTA, gradual dose reduction to a minimum dose of one capsule at night (5 mg olanzapine or matching placebo per day) may occur in consultation with the participant’s treating doctor and study psychiatrist. All dosage changes for each participant will be reported. Specific data to determine dose range in this setting is not available. We therefore chose this dose range based on Australian regulatory approval of olanzapine dosages of 5–20 mg to treat other neuropsychiatric conditions, such as schizophrenia and bipolar I disorder [46].

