### Sample size

Simulation studies by Teare et al. [71] indicate that small studies (less than 50 participants, 25 per group) do not provide realistic estimates of results, indicating that group sizes should be at least 25, and that preferably a minimum of 35 participants per group be employed where possible.

Although it did not specifically include the ABS, a recent systematic review [41] reported standardised mean differences (i.e. Cohen’s *d* or the difference in group means divided by the pooled group standard deviation) in 2-h and 24-h post-administration levels of agitation between intramuscular olanzapine and placebo ranging from 0.36 to 1.93. In regard to other populations, a study of agitation levels in patients with schizophrenia following administration of intramuscular olanzapine or placebo found a standardised mean difference of 1.27. The minimal clinically important difference for improvement in irritable/aggression scale scores in TBI [68] is equal to a standardised mean difference of 0.50, the conventional Cohen medium effect size, with a large Cohen effect size being defined as a standardised mean difference of 0.80. Given the above prior findings, a large effect size would be expected. Using the Stata 15 power and sample-size procedure, we calculated the required sample size to detect a standardised mean difference/effect size of 0.80 (e.g. 0.80 of the standard deviation of 4.1 for mean daily ABS score at outcome reported in the pilot study of McKay et al. [26], *n* = 125) with a statistical power of 0.80 and a 2-tailed alpha of 0.05. Results indicated a required sample size of 26 patients per group, for a total of 52 patients.

A sample size of 26 patients per group, or 52 in total, exceeds the lower threshold of 50 patients identified by Teare et al. [71] and is clinically practical. Assuming 10% attrition, 29 patients (26/(1–0.10) = 28.9, conservatively rounded to 29) per group would be required, for a total of 58 patients, in order to complete the study with 52 patients.

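### Day 0 is both baseline and the first day of the primary ABS window, so a wholly or partly pre-dose rating counts as outcome and dilutes the effect, materially only when PTA is short

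*Protocol article*

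**What the plan says.** All references are to the protocol article.

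- **Baseline section.** It is headed as day 0. It lists a baseline ABS and WPTAS, taken from the medical record after eligibility is confirmed and the patient is randomised.
- **Treatment section.** It is also headed as starting on day 0: "The treatment period will last from day of completion of baseline assessments until the patient is deemed to have emerged from PTA", or until six months have passed.
- **Primary outcome.** The groups are compared on mean daily ABS during PTA, and "This outcome will include all daily ABS assessments throughout the treatment period". No rating made before the first capsule is excluded. On the scale itself: "Completion involves the observer rating the presence of 14 agitated behaviours based on the past 8-h period".
- **Intervention, randomisation and allocation.** The first titration step is "one capsule at night (5 mg olanzapine or matching placebo per day".
- **Table 1.** The ABS has one mark under baseline/randomisation and another under the treatment period.
- **Statistical methods and Secondary outcomes.** The primary mixed model is said to account for PTA duration; baseline ABS is not named there. Discharge ABS, in contrast, is adjusted for the ABS at the start of treatment. The mean WPTAS runs from the first day of treatment and is adjusted for the baseline WPTAS.

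The article does not give the time of day of the ABS rating, the day of the first capsule, or the expected number of treatment days.

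**The concern.** Taken together, these sections put day 0 inside the primary window. A rating made on day 0 cannot lie wholly after the first capsule: even one made at midnight looks back to 16:00, and the capsule is given at night. So the score is wholly or partly pre-dose, whatever the rating time.

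By randomisation, a wholly pre-dose score has the same expected value in both arms. Averaging it with the later scores pulls the arm means together. The pull is greatest in patients who leave PTA quickly, where one day is a large share of the average.

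The trial has little power to spare, and the Statistical methods section judges clinical significance against half a pooled SD, so the dilution also bears on that reading. As an illustration, a true post-dose difference of 0.55 SD over ten ratings would be estimated at about 0.55 × 9/10 = 0.495 SD, just under the threshold.

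**Working it through.** **Inputs from the Sample size section.** The target is a "standardised mean difference/effect size of 0.80", with the "standard deviation of 4.1 for mean daily ABS score at outcome", "with a statistical power of 0.80 and a 2-tailed alpha of 0.05". The stated result is a "required sample size of 26 patients per group, for a total of 52 patients", raised to 29 per group for 10% attrition. In ABS points the target is 0.80 × 4.1 = 3.28.

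**Reproducing the plan's figure.** For a two-sample t-test with n per group, the noncentrality is d × √(n/2) on 2n − 2 degrees of freedom. With d = 0.80 and n = 26 it is 0.80 × √13 = 2.88 on 50 degrees of freedom, and power is 0.807. With n = 25, power is 0.791. So 26 per group is the smallest size that reaches 0.80. Attrition: 26/0.90 = 28.9, rounded up to 29. The plan's figures reproduce.

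**Dilution by one pre-dose day.** Let a patient have T equally weighted daily ratings including day 0, with an expected difference of zero on day 0 and d on the other T − 1 days. The difference in patient means is then

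d × (T − 1)/T, a relative loss of 1/T.

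A day-0 rating that is only partly pre-dose loses less, so 1/T is the upper limit for that one day.

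**Assumptions.** T is the same for all patients, the SD stays at 4.1, and 0.80 is the effect on post-dose days. The article does not give T. The Background describes PTA as lasting from days to months, so a range is shown.

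| T | Loss (1/T) | Diluted effect (SD) | ABS points | Power, 26 per group |
|---|---|---|---|---|
| no pre-dose day | 0 | 0.80 | 3.28 | 0.81 |
| 5 | 20% | 0.80 × 4/5 = 0.640 | 2.62 | 0.62 |
| 10 | 10% | 0.80 × 9/10 = 0.720 | 2.95 | 0.72 |
| 14 | 7% | 0.80 × 13/14 = 0.743 | 3.05 | 0.75 |
| 30 | 3% | 0.80 × 29/30 = 0.773 | 3.17 | 0.78 |
| 90 | 1% | 0.80 × 89/90 = 0.791 | 3.24 | 0.80 |

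**Sensitivity to the SD.** An extra day also slightly lowers the SD of a patient's mean. With within-patient correlation ρ between days, the variance of a mean of m days is proportional to v(m) = ρ + (1 − ρ)/m, and the diluted effect is multiplied by √(v(T − 1)/v(T)). For ρ from 0.3 to 0.7, power is 0.63 to 0.65 at T = 5, about 0.75 at T = 14 and 0.78 at T = 30. The picture does not change.

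**The case against.** The case against has several parts.

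- **Table 1 separates the two scores.** Baseline ABS comes from the record, and the ABS is already rated daily before enrolment, so the baseline value may be an earlier rating. This stands to the extent that the article does not force one score into both roles. It does not take the day-0 rating out of the treatment period, which by its own definition begins that day.
- **A window convention belongs in the analysis plan.** Often it does. Here, though, the article fixes the window by taking all ratings of a period that starts on the baseline day. An analysis plan that dropped day 0 would depart from that text.
- **The 0.80 may already describe the averaged endpoint.** The SD it is scaled on is that of the mean daily score. If so, planned power is unaffected, and dropping day 0 would be a gain above it. This stands as a limit on the power figures.
- **Titration also weakens the early days.** Steps come every 3 to 4 days, so the first treated days may carry only part of the effect. That is true, but those days belong to the treatment being tested; a rating before the first capsule does not.
- **The planned analysis is a mixed model, not a t-test on means.** The factor (T − 1)/T is exact only for simple patient means with equal T. With unequal PTA durations the dilution would be some weighted average over patients, so the figures show scale only.

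A reader might infer that every patient contributes an agitated score known to precede the first capsule. The documents do not support that. They give no rating time and no first-dose day, and the Recruitment section foresees agitation ending between randomisation and dosing. The dilution does not depend on the day-0 score being high, only on its having no expected difference between arms.

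**Conclusion.** The point holds as a flaw in a stated window. Day 0 is given to both baseline and treatment, and the primary outcome takes every rating of the treatment period, so on the text as written a wholly or partly pre-dose score counts as outcome. It shrinks the arm difference by up to about 1/T.

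The size depends on T, which is assumed. At T = 30 or more, power falls by about 3 percentage points or less. At two weeks it is about 0.75, and below that the loss is material. It would be wrong to conclude that the trial's power is 0.62: that needs every patient to have only five ratings, and nothing in the article says so. It would also be wrong to infer a bias in favour of olanzapine, since the pull is toward no difference.

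Severity is minor to moderate. The correction is a free improvement.

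**What to change.** In the Treatment and Primary outcome sections, define day 0 as the day of randomisation and baseline, and start the primary ABS window on the following day for all randomised patients. Use one rule for everyone, dosed or not. Starting at the first capsule for dosed patients and at randomisation for the others would create two start rules, one of them tied to a post-randomisation event. A uniform start keeps the intention-to-treat comparison. Any later delay to the first capsule then stays in the window as part of the treatment as delivered.

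Use the last ABS up to randomisation, and in any case before the first capsule, only as baseline. Enter it as a covariate in the primary model, as is already planned for discharge ABS.

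Apply the same start day to two secondary outcomes:

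- **Mean WPTAS**, so that one score cannot be both part of the outcome and the baseline it is adjusted for.
- **Count of clinically agitated days**, where the same expected pre-dose day in both arms would pull the ratio from a count model toward 1.

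The cost is a sentence or two in the outcome definitions. The ABS is already rated daily, so no new data are needed and no clinical rule changes. The article reports a recruitment status of 5 and blinded investigators, so at that stage the change could be made without knowledge of results by arm.

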#### Secondary outcomes

To examine the safety of olanzapine administration in PTA patients: Difference between olanzapine and placebo groups’ mean number of AEs (as captured via trial bloodwork, Adverse Events Questionnaire, Simpson-Angus Scale, measures of weight, BP, HR, WC) during PTA.To determine whether olanzapine treatment reduces the number of clinically agitated days during PTA: Difference between olanzapine and placebo groups’ mean number of clinically agitated days (ABS score > 21) during PTA.To determine whether olanzapine treatment alters level of agitation at hospital discharge: Difference between olanzapine and placebo groups’ mean ABS score at discharge, controlling for ABS score at treatment commencement.To determine whether olanzapine treatment alters level of cognition in PTA: Difference between olanzapine and placebo groups’ mean levels of PTA as measured using the WPTAS [44, 45], controlling for WPTAS score at baseline. Mean scores will encompass daily assessments of the WPTAS throughout the treatment period, from first day of treatment until emergence from PTA (defined as the first of three consecutive days on which a score of 12 on the WPTAS is obtained). The WPTAS is commonly used in Australia to assess PTA. Seven items on the WPTAS assess orientation to time, person and place, and five assess anterograde memory (therapist face, name and three picture cards). Good construct validity and inter-rater reliability have been demonstrated [45, 61]. Nurses and clinical neuropsychologists who administer the WPTAS at Epworth HealthCare are trained in its use.To determine whether olanzapine treatment alters PTA duration: Difference between olanzapine and placebo groups’ mean number of days in PTA (from date of injury until emergence from PTA based on three consecutive scores of 12 on the WPTAS).To determine whether olanzapine treatment alters cognitive performance following PTA emergence:
Difference between olanzapine and placebo groups’ mean total words recalled over five trials on the RAVLT [50]. The RAVLT is a 15-word cognitive list learning task. This test is sensitive to memory impairments in TBI populations [62] and has good psychometric properties [63].Difference between olanzapine and placebo groups’ mean number of items completed on the SDMT [51]. The SDMT is a test of processing speed, requiring transcription of numbers corresponding with symbols from a key over 90 s. Use of the oral version of this test will avoid effects of motor weakness on performance. The oral SDMT has excellent psychometric properties [64].Difference between olanzapine and placebo groups’ mean number of errors on the SDMT.

Epworth HealthCare clinical neuropsychologists who will administer these measures are trained and experienced in their use.
7.To determine whether olanzapine treatment alters length of inpatient hospital stay: Difference between olanzapine and placebo groups’ mean length of inpatient hospital stay, measured in days from day of admission until day of discharge from inpatient care.8.To determine whether olanzapine treatment alters functional independence at discharge and 3-month follow-up:
Difference between olanzapine and placebo groups’ mean scores on the FIM [52] at hospital discharge. The FIM is a measure of motor and cognitive functional status. It has good reliability [65] and is well validated in brain injury populations [66]. This measure will be completed by the participant’s treating occupational therapist, who is trained in its use.Difference between olanzapine and placebo groups’ mean scores on Mental Component Summary (MCS) and Physical Component Summary (PCS) subscales of the SF-12 at hospital discharge. The SF-12 measures the patient’s view of their health-related quality of life. PCS and MCS scores are derived. The SF-12 is commonly used in TBI samples [67] and has excellent psychometric properties in the general population [53].Difference between olanzapine and placebo groups’ mean scores on the MPAI-4 [55] at follow-up. The MPAI-4 assesses physical, cognitive, emotional, behavioural and social sequelae of TBI and obstacles to community integration on 3 subscales: Ability Index, Adjustment Index and Participation Index. It has strong psychometric properties [68], is used widely in TBI research and is more sensitive to disability after return to the community than the FIM [63]. The MPAI-4 will be completed via telephone interview with the study participant’s MTDM. Traumatic brain injury patients often present with issues with reduced self-awareness and memory. By having those knowledgeable about the patient’s functional independence complete this measure, problems with self-awareness and memory within this population are circumvented.9.To evaluate the cost-effectiveness of olanzapine administration:
Total cost per patient to 3-month follow-up, calculated by combining standard unit costs [69] with patient-level data on health service utilisation to 3-month follow-up and estimates of productivity gains/losses. Health service utilisation will be estimated based on medical record indicated medication use, therapy hours, length of inpatient hospitalisation, special nursing care and PDHSUQ as completed by the patient and their MTDM at 3-month follow-up. Once again, data collection from the point of view of the MTDM at this time point aims to overcome difficulties associated with poor self-awareness and memory in TBI patients. The PDHSUQ has been designed for the purposes of this trial to assess participants’ post-discharge use of medications, allied health services, psychologists or counsellors, general practitioner visits, use of paid or unpaid carers and admissions to hospital. Productivity gains/losses will be estimated based on inpatient length of inpatient hospitalisation, FIM scores at discharge and MPAI-4 scores at 3-month follow-up.Incremental cost of olanzapine and environmental management versus placebo and environmental management, calculated per patient to 3-month follow-up as the (adjusted) difference between olanzapine and placebo groups’ mean total cost per patient to 3-month follow-up.Incremental cost per unit improvement on the ABS (mean daily ABS scores for olanzapine and placebo groups during PTA).Incremental cost per point improvement on the FIM between PTA emergence and hospital discharge (mean scores for olanzapine and placebo groups).Incremental cost per quality-adjusted life year gained (mean scores for olanzapine and placebo groups calculated using the SF-12 SF-6D utility index scores and derived using recently published Australian weights [70]).

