Upon emerging from PTA as judged by a score of 12/12 on the WPTAS on three consecutive days, olanzapine will be tapered at a rate deemed appropriate by study doctors. Dose reduction or rechallenge may be undertaken in the setting of an adverse event (AE). Intervention may also be discontinued in the following circumstances: (1) following 6 months in PTA, (2) withdrawal of MTDM consent, (3) due to medical considerations or (4) escalation of agitation to an unmanageable level, resulting in physical aggression posing threat of harm to staff or property.

To maximise compliance, study staff will regularly check that treatment has been administered as prescribed by reviewing the participant’s medical chart. Study staff will also complete a treatment log, recording whether dosages have been administered, and dosage amount.

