### Harms

A DSMC has been established. The DSMC is independent of the study team and consists of a psychiatrist (chair), neuropsychiatrist and biostatistician. The DSMC will monitor outcomes and be informed of serious AEs and withdrawals. The DSMC will advise study staff on (1) dose reduction, rechallenge or withdrawal in response to AEs, in consultation with the treating doctors; (2) withdrawal of participants due to escalation of agitation to an unmanageable level, resulting in physical aggression posing threat of harm to staff or property, in consultation with study psychiatrist; and (3) necessity of emergency unblinding in response to an AE. No further DSMC charter exists or is currently planned to be developed. The DSMC will not engage in interim analyses. Should a decision need to be made regarding early trial termination, this decision will be made jointly between study principal investigators and the DSMC.

Potential AEs will be monitored in the following ways:

1. Medical information—Weekly measures of weight, BP, HR and WC will be conducted by nursing staff at baseline, weekly throughout the treatment period and following emergence from PTA. Plans for the collection, laboratory evaluation and storage of blood samples are detailed in the provided (Additional file 1).

2. Blood tests—Blood tests assessing fasting lipids, fasting glucose, HBA1C and creatinine will occur at several time points: at baseline, upon the participant’s first score of 12 on the WPTAS (an early indicator of emergence from PTA), monthly throughout the treatment period and following emergence from PTA. Plans for the collection, laboratory evaluation and storage of blood samples are detailed in the provided Appendix: Biological Specimens.

3. The SAS [49]—This scale will be completed by the participant’s treating physiotherapist at baseline and weekly throughout the treatment period. The SAS is a rating scale for extrapyramidal system disturbance widely used to assess side effects related to antipsychotic drug use. It has well-established psychometric properties [49].

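### Prompted adverse-event capture and the AE count stop at PTA emergence, while study capsules continue through a taper of unstated length

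*Protocol article*

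**What the plan says.** **Outcome window.** The first item under Secondary outcomes is the difference between groups in "mean number of AEs (as captured via trial bloodwork, Adverse Events Questionnaire, Simpson-Angus Scale, measures of weight, BP, HR, WC) during PTA".

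**Treatment period.** The Treatment section states: "The treatment period will last from day of completion of baseline assessments until the patient is deemed to have emerged from PTA", with a six-month cap. It dates emergence to the first of three consecutive days with a full WPTAS score.

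**Dosing after emergence.** Under Intervention, randomisation and allocation, once the three full scores have been obtained, "olanzapine will be tapered at a rate deemed appropriate by study doctors". The Post-PTA section repeats this: "treatment will be titrated down as appropriate". The top of the dose range is 20 mg per day. Reduction towards 5 mg per day is allowed during PTA once the ABS score falls below 22.

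**Schedules of the four AE sources (Harms).**
- Weight, BP, HR and WC: at baseline, then "weekly throughout the treatment period and following emergence from PTA".
- Blood tests: at baseline, at the first WPTAS score of 12, and "monthly throughout the treatment period and following emergence from PTA".
- Simpson-Angus Scale: by the "treating physiotherapist at baseline and weekly throughout the treatment period".
- Adverse Events Questionnaire: weekly within the treatment period, covering nine listed symptoms.

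**What else continues.** Under Harms, all serious AEs go to the DSMC, AEs already recorded are followed until they settle, and telephone follow-up is provided for AEs that outlast the admission.

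**The concern.** Safety is the first secondary aim (Background), and the protocol gives the lack of good data on harms as one reason for the trial. The taper is part of the protocol's own dosing, so it is time on study product. If the two instruments that prompt for symptoms and extrapyramidal signs stop before the capsules do, the AE comparison covers only part of the time on drug. Events that begin as the dose changes or is withdrawn would come to light only if they were serious or if someone volunteered them. Unprompted reports of that kind cannot be compared with the prompted weekly count made before emergence.

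**Working it through.** **Step 1: set the schedules beside the dosing.**

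| Item | Up to emergence | After emergence, while capsules continue |
|---|---|---|
| Study capsules | yes | yes, until confirmed and then tapered |
| AE questionnaire (9 symptoms) | weekly | none scheduled |
| Simpson-Angus Scale | baseline and weekly | none scheduled |
| Weight, BP, HR, WC | baseline and weekly | scheduled |
| Blood tests | baseline, monthly, first WPTAS 12 | scheduled |
| AE-count outcome | counted | outside the stated window |

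Of the four AE sources named in the outcome, two have no scheduled completion after emergence. The Harms section adds a post-emergence assessment for the other two, so the difference is written into the text. Table 1 agrees, but it also marks treatment administration only in the PTA column and so cannot settle the matter. The finding rests on the Treatment and Harms sections.

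**Step 2: when does the gap open?** Emergence is dated to day 1 of three full-score days, and the taper follows the third. If the window closes on the dated day, two days of dosing (days 2 and 3) already lie outside it before any taper. If it closes on the day emergence is confirmed, only the taper lies outside.

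**Step 3: size, by assumption only.** The protocol gives no taper length. Assume the two days above, a taper of L days, and P days on drug in PTA. The share of on-drug days outside the window is (2 + L)/(2 + L + P).

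- No taper (for example, already on 5 mg): L = 0 gives 2/16 = 12.5%, 2/30 = 6.7% and 2/44 = 4.5% for P = 14, 28 and 42.
- Short taper: L = 3 gives 5/19 = 26%, 5/33 = 15% and 5/47 = 11%.
- From 20 mg through 15, 10 and 5 mg, borrowing the 3 to 4 days between escalations: L = 3 × 3 = 9 to 3 × 4 = 12. L = 9 gives 11/25 = 44%, 11/39 = 28% and 11/53 = 21%. L = 12 gives 14/28 = 50%, 14/42 = 33% and 14/56 = 25%.

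L and P are both assumed. The spread shows only that the share cannot be fixed from the document.

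**Step 4: cost of closing the gap.** Weekly completions plus one at the last capsule, for a taper of T days, number floor((T − 1)/7) + 1 = ceil(T/7). That is 1 for T = 1–7, 2 for T = 8–14 and 3 for T = 15–21. If all 58 participants reach the taper, the Simpson-Angus totals are at most 58, 116 and 174. A participant discharged before the last capsule needs up to one more questionnaire, so the questionnaire totals are at most 116, 174 and 232.

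**The case against.** The strongest reply is that the window fits the aim. The objective concerns safety in patients in PTA, and a PTA-limited AE count answers that question. This is a choice of on-treatment window, and nothing in the objective contradicts it. That stands, and it is why the point is an improvement and why the PTA count should be kept.

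A reader might infer that safety monitoring ceases at emergence. The Harms and Post-PTA sections do not support that. Serious events, events already recorded, blood tests and vital signs are all still covered, a blood sample is due at the first WPTAS score of 12, and ABS ratings continue daily for two weeks.

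A reader might also infer that the post-emergence blood and vital-sign results are never used. That too goes beyond the text. Statistical methods plans count regression for AEs and for further safety measures without a PTA limit, so these results may be analysed there. An AE start date is recorded, and the outcome does not say whether onset or detection decides membership. A metabolic change found shortly after emergence could be assigned to PTA. What remains is that the outcome wording does not clearly include these results in the AE count.

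It could be argued that the treatment period is meant to include the taper. The Treatment section defines it otherwise and the taper is described again under Post-PTA. Even on that reading, the outcome wording would leave taper-onset events out of the count.

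Finally, an article may leave detail to the full protocol. Here, however, the window, the period and each instrument's schedule are all stated.

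**Conclusion.** The point holds in a narrow form. New non-serious symptoms or extrapyramidal signs that start after emergence, while capsules are still being given, have no prompted capture and are not in the AE count. The status of post-emergence blood and vital-sign changes in that count is unclear.

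The amount of exposure involved is unknown. It would be tempting to conclude that a large part of exposure goes unobserved, or that participants generally taper from 20 mg per day. The document supports neither: 20 mg is the ceiling, earlier reduction to 5 mg is allowed, and no taper length is given. The gap may be small. It affects the first secondary aim but not the primary outcome or the sample size. Minor to moderate priority.

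**What to change.** Define the AE window as first capsule to last taper capsule. Continue the existing weekly questionnaire and Simpson-Angus Scale to the last capsule, with one completion of each at that point. If discharge comes first, complete both at discharge and do a final questionnaire by telephone at the last capsule. The present telephone provision covers only AEs that are still continuing, so it needs a sentence extending it to new ones. State that clinically significant post-emergence changes in bloods, weight, BP, HR and WC count as AEs in the outcome. Report the PTA-only count beside the extended one.

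The cost is about ceil(T/7) extra completions of each form per participant, plus up to one more questionnaire where discharge precedes the last capsule. This takes time from the treating physician with study staff, and from the treating physiotherapist. No new instrument is needed. One limit remains: extrapyramidal signs that first appear after discharge would still go unrated.
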